## Study Site

This study will be conducted in the offices of Vielight Inc. at [name] in the downtown Toronto region. This site has been setup to meet the requirements of the EEG system.

# SUBJECT ELIGIBILITY

## Inclusion Criteria

1. Present valid government identification demonstrating age of 60 years or older
2. Capable of speaking English in order to comply with study procedures
3. Capable of reading English in order to complete Informed Consent form and online screening survey

## Exclusion Criteria

1. Unable/unwilling to sign Informed Consent form
2. Mini Mental State Examination (MMSE) score of <27
3. Current major psychiatric or neurologic disease
4. History of stroke or seizures
5. Medical conditions uncontrolled by stable therapy

# STUDY EXECUTION

## Subject Recruitment

Subjects will be recruited from the Greater Toronto Area through recruitment advertisements placed online on sites such as Craigslist or Kijiji and via social media sites including Facebook. Advertisements in the form of posters in the local area surrounding the study site or in newspapers such as NOW! or Eye Weekly may also be used to recruit prospective subjects. Any advertisements will be approved by an Institutional Review Board. A total of 20 subjects are anticipated to complete this study.

## Preliminary Eligibility Assessment

Eligibility screening will be conducted through an online screening form providing a short description of the study and requesting non-medical information. Questions will be related to the inclusion criteria in section 3 above as well as with regards to their ability to comply with study procedures (eg. willingness to remove any religious clothing or wigs to accommodate the EEG cap).

## Study Visit Procedures

**FIRST STUDY VISIT**

A) Study description and Informed Consent

- Study staff will explain the purpose of the study to the participant and what study participation will involve.
- Information must be given in both oral and written form.
- Subjects will be provided a copy of the *Informed Consent Form,* and given as much time as necessary to make an informed decision regarding participation.
- The subject information advises the participant that they are free to refuse their participation in or withdraw from the study at any time.
- The subject will be encouraged to ask questions.
- The investigator or other study staff will then obtain and document informed consent from the participant.
- The subject will be given copies of the signed *Informed Consent Form*.
- If consent is declined, the subject's reason for declining (if provided) will be recorded in the screening log and CRF

B) Assessment of eligibility criteria

- Following consent, study staff will reassess eligibility captured during online screening and record these on the study Case Report Form (CRF).
- Study staff will also confirm the following exclusion criteria and record these on the study Case Report Form (CRF):
  1. No current major psychiatric disorder or neurologic disease
  2. No history of stroke or seizure
  3. No other medical conditions uncontrolled by stable therapy
- Study staff will then conduct the MMSE to determine if the participants score is above 27 (ie. cognitively healthy) and record this on the study Case Report Form (CRF).
- INCIDENTAL FINDINGS: If the subject has a MMSE score of 23 or lower, they will be informed that their score indicates potential cognitive impairment; however, this finding may be erroneous. Subjects will be encouraged to visit a physician in order to be properly assessed for cognitive impairment.
- If the subject does not satisfy eligibility criteria, the subject will not be enrolled and the CRF will indicate the reason for exclusion. A screening log will be maintained listing all subjects screened for the study and will document the reasons for non-participation of non-enrolled subjects.

C) Acquisition of EEG recordings

- Subject will be asked to sit in a comfortable chair, with their back supported and their legs and ankles uncrossed with feet flat on the floor
- Study staff will record any relevant subject details (physical characteristics and demographics) in the Case Report Form. These include but are not limited to: the Subject’s date of birth (YYYY-MM-DD), sex, weight, height, etc.
- Study staff will place the saline-rinsed EEG electrode cap on the subject and may apply additional saline to individual electrode locations in order to ensure good conductivity
- Once the electrode cap is producing reliable readings, the subject will be asked to remain still and quiet with their eyes closed for an initial 10 min Rest-EEG recording
- At the completion of the 10 min recording, study staff will then place the Vielight Neuro Gamma device or Sham device on the subject, as shown in Figure 2 above.
- Study staff may then re-apply additional saline to individual electrode locations in order to ensure good conductivity
- Once the electrode cap is producing reliable readings, the subject will be asked again to remain still and quiet with their eyes closed for a 20 min Rest-EEG recording
- At the completion of the 20 min recording, study staff will then remove the Vielight Neuro Gamma device or Sham device and again re-apply additional saline to individual electrode locations in order to ensure good conductivity
- Once the electrode cap is producing reliable readings, the subject will be asked to remain still and quiet with their eyes closed for a final 10 min Rest-EEG recording

**SECOND STUDY VISIT**

The second study visit will be a replication of Part C of the first visit. At the conclusion of the visit, the subject will be provided financial compensation of $100 CAD for the study.

# STUDY VISIT EQUIPMENT

## Devices and Procedural Purposes

| **Device** | **Purpose** |
| --- | --- |
| Vielight Neuro Gamma | Device being evaluated for effect on neural activity |
| BrainMaster Discovery 20 System | Quantitative EEG system with recording electrode cap |

## Device Safety

Vielight Neuro Gamma: The controller houses three 1.5V NiMH batteries (1900 mAh each) and the controlling electronics for the Neuro Gamma. Both the Headset and Nasal Applicator are connected to the controller with connectors that prevent them from being incorrectly inserted. A single button initiates a software controlled 20-minute therapy – automatically timed but can be discontinued by pressing the button a second time. The maximum power output density to the nasal mucosa is 25 mW/cm^2^ with a 50% duty cycle (total energy delivered per session = 15 J). The maximum power output density to the scalp is 100 mW/cm^2^ with a 50% duty cycle for the posterior band LEDs and 100 mW/cm^2^ with a 50% duty cycle for the anterior band LED (total energy delivered per session = 225 J). All LEDs are well under the exposure limits established by IEC 62471:2006 - *Photobiological safety of lamps and lamp systems*..

BrainMaster Discovery 20 System: The BrainMaster Device does not produce any electro-magnetic fields and does not interfere with the operability of other devices The unit is entirely powered by the USB interface, eliminating the need for batteries, while maintaining subject safety.

# STATISTICAL PLAN AND METHODS

## Planned Analysis

The primary endpoint for this study will be the change from baseline in overall power spectral density between active and sham session. To statistically determine a significant difference a repeated measures ANOVA with treatment as the within-subject measure will be utilized.

Additional exploratory analysis of a variety of measures obtained from the EEG recording will be conducted post-hoc.

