## Study Device: Vielight Neuro Gamma

The Vielight Neuro Gamma device is a portable, wearable, low-level light delivery device that administers near-infrared light to the brain trans-cranially and intra-nasally and is intended to enhance mental acuity as part of general wellness. The device, shown below, consists of a controller (1), a Nasal Applicator (2), and a Head Set (3).

[figure not shown]

Figure 1. Vielight Neuro Gamma device

The Vielight Neuro Gamma delivers painless, non-invasive, non-thermal, non-laser, pulsed (40 Hz; 50% duty cycle), near-infrared light (810 nm wavelength) through 5 non-laser light emitting diodes (LEDs) over a 20 minute session. The device is powered by three rechargeable NiMH batteries. As shown below, one of the Vielight Neuro Gamma LEDs is placed inside the nose for intranasal transmission of light energy and the remaining four LEDs are positioned over the skull for transcranial transmission.

| [figure not shown][figure not shown]  Figure 2. Placement of Vielight Neuro Gamma device |
| --- |

##

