## Study Endpoints

Detailed information about endpoint calculation is provided in Section 6 Statistical Plan and Methods.

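### The primary endpoint does not say which of the two post-baseline EEG recordings it uses, and the one made with the device in place has no stated safeguard against 40 Hz device pick-up

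*Protocol*

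**What the plan says.** The Study Endpoints section of the protocol gives no definition of its own. It says: "Detailed information about endpoint calculation is provided in Section 6 Statistical Plan and Methods". Section 6.1, Planned Analysis, then reads: "The primary endpoint for this study will be the change from baseline in overall power spectral density between active and sham session". The test is described as follows: "a repeated measures ANOVA with treatment as the within-subject measure will be utilized". The synopsis repeats the same endpoint and method.

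Under Study Visit Procedures, part C, each session has three resting recordings:

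- before the device is placed: "with their eyes closed for an initial 10 min Rest-EEG recording"
- with the active or sham device in place: "with their eyes closed for a 20 min Rest-EEG recording"
- after the device is removed: "with their eyes closed for a final 10 min Rest-EEG recording"

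The device section describes the output as "pulsed (40 Hz; 50% duty cycle), near-infrared light (810 nm wavelength", delivered over a 20-minute session, and the synopsis says the devices are used while the EEG is recorded. Under Device Safety, the only statement on interference is that the EEG unit does not disturb other devices. The sham is described only as something that neither the subject nor the EEG technician can tell from the active device.

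**The concern.** A change from baseline needs a baseline and one defined later measurement. The baseline can be identified, but the later measurement cannot, because two recordings qualify. The only factor named for the ANOVA is treatment, so the text does not say whether one recording is used, the two are pooled, or recording enters as a further factor. The section that is said to hold the calculation does not hold it. A choice made after seeing the data would give two chances of a positive result.

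The two recordings also differ in kind. One is made while a device pulsed at 40 Hz sits on the head with the EEG electrodes, and the other with the device off. The trial asks whether near-infrared light reaches the brain and has a reliable effect there. If electrical pick-up from the device entered the EEG in active sessions and not in sham sessions, it could produce a difference in power spectral density (PSD) with no light reaching the brain. The protocol's interference statement covers the EEG unit acting on other devices, not the reverse.

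**Working it through.** **Sample size.** The protocol's 20 subjects rest on a literature review with no alpha, power, effect size or standard deviation, so there is no planned figure to reproduce.

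**Step 1: is the recording fixed anywhere?**

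| Place in the protocol | What it fixes | What it leaves open |
|---|---|---|
| Study Endpoints | Refers to Section 6 | Everything else |
| Synopsis and 6.1 | Change from baseline, overall PSD, active against sham | Recording, frequency range |
| 6.1, model | Treatment as within-subject factor | How two post-baseline recordings enter |
| Study Visit Procedures, part C | Three recordings: 10, 20 and 10 minutes | Which of the last two is the endpoint |
| Title and rationale | A real-time aim, which suggests the 20-minute recording | Any link from that aim to the endpoint |

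**Step 2: cost of an open choice.** Inputs: two candidate recordings (part C); two-sided alpha 0.05 (assumed); correlation r between the two test statistics (assumed). With no true effect,

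P(at least one significant) = 2 × 0.05 − P(both significant),

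where P(both significant) is the bivariate normal probability that both |Z| exceed 1.96.

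| r | P(both) | P(at least one) |
|---|---|---|
| 0 | 0.0025 | 0.0975 |
| 0.3 | 0.0049 | 0.0951 |
| 0.5 | 0.0093 | 0.0907 |
| 0.7 | 0.0165 | 0.0835 |
| 0.9 | 0.0296 | 0.0704 |

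A simulation of two correlated paired t-tests with n = 20 (200,000 runs), equivalent to a two-level repeated measures ANOVA, agrees: 0.095, 0.090, 0.084 and 0.071 at r = 0.3, 0.5, 0.7 and 0.9. If a duration-weighted average of the two recordings is allowed as a third option, the rates are 0.105, 0.097, 0.087 and 0.072. With one recording named in advance, the rate is 0.05.

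**Step 3: what pick-up would do if it occurred in active sessions only.** The protocol gives no size for it, so the shift d is an assumption, in standard deviations of the paired active-minus-sham difference. With no neural effect and n = 20, the paired t statistic is noncentral t with 19 degrees of freedom and noncentrality d × √20. The two-sided 5% critical value is 2.093.

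| d (assumed) | d × √20 | P(significant) |
|---|---|---|
| 0.25 | 1.12 | 0.19 |
| 0.50 | 2.24 | 0.56 |
| 0.66 | 2.95 | 0.80 |
| 1.00 | 4.47 | 0.99 |

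A consistent shift is not averaged away by adding subjects. If the sham drives the same 40 Hz electronics with only the light blocked, pick-up would largely cancel and d would be near zero.

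**The case against.** Four objections deserve an answer.

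*The frequency range, artefact handling and time factor belong in a statistical analysis plan, which may exist.* This is largely right, and the absence of those details alone would be no finding. What stands is narrower: the protocol says its own Section 6 contains the calculation, and it does not. Nor does naming treatment as the within-subject measure rule out a recording factor, so it would be too strong to say that the analysis must pick or pool.

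*The intended recording is signalled.* The title and rationale speak of real-time effects. That makes the 20-minute recording the likelier reading, but nothing ties the endpoint to it, and the device-off recording is an equally valid change from baseline.

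*The study is exploratory.* The sample-size section describes an initial study for estimating effect sizes. That lowers the stakes, but the Study Objective and 6.1 still plan a significance test, and the estimates are meant to inform confirmatory studies.

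*Pick-up is conjecture.* A reader might infer that every active session is biased by electrical pick-up and no sham session is. The documents do not support that. They say the light is pulsed at 40 Hz. They do not describe the drive electronics, shielding, coupling to the electrodes, the EEG frequency range or the sham's electrical behaviour. The technician must obtain reliable readings and is said to be unable to tell the devices apart, which weighs against gross active-only pick-up but does not exclude a small amount. This objection stands, so pick-up is an unaddressed possibility and not a demonstrated fault.

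**Conclusion.** The endpoint is incompletely defined on the protocol's own terms: two post-baseline recordings exist, neither is named, and the cross-reference to Section 6 leads to no calculation. If the choice is left until the data are seen, the type I error is about 7.0% to 9.5% in place of 5%, for correlations of 0.9 to 0.3. Two recordings from one sitting that share a baseline may be highly correlated, so the lower end should be taken seriously. An analysis plan that fixes the recording in advance would remove this inflation, but the protocol's statement would still need correcting.

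The pick-up risk is secondary and conditional. It matters only if the device couples into the EEG, the analysed range includes the affected frequencies, and the sham does not produce the same signal. None of these is stated either way. The point should be corrected before analysis, but it does not invalidate the design.

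**What to change.** In Section 6.1:

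1. Name one primary contrast. The 20-minute during-device recording minus the initial 10-minute recording, active against sham, matches the real-time aim. Name the change to the device-off final 10-minute recording as secondary.
2. State whether the sham drives the same 40 Hz electronics as the active device.
3. Report the primary contrast with and without a narrow band around 40 Hz and its harmonics within the analysed range, treated identically in both sessions, and show 40 Hz power separately. State the width of the band in advance.
4. Do not attribute to neural activity an effect that disappears when that band is excluded, unless the sham is shown to be electrically equivalent.

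Requiring the final recording to point the same way before calling an effect neural is not recommended. Given a false-positive primary result, the two would agree in sign with probability 0.77, 0.91, 0.99 and above 0.99 at r = 0.3, 0.5, 0.7 and 0.9 (bivariate normal), so the rule filters little. It would also reject a true effect present only during stimulation.

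The cost is a few sentences and a little more analysis, with no change to the 20 subjects, the visits or the procedures. The downside is that a genuine response confined to 40 Hz during stimulation would be reported with a caveat.

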# STUDY SYNOPSIS

| Study Title | Evaluating the effect of pulsed near infrared transcranial and intranasal photobiomodulation on real-time EEG signals in older adults at rest |
| --- | --- |
| Study Objective | To evaluate whether pulsed near infrared transcranial and intranasal photobiomodulation produces a reliable effect on neural activity in older adults. |
| Methodology | Double-blind, prospective, crossover |
| Study Duration | Two session evaluation |
| Number of Subjects | Maximum of 20 older adults |
| Major Inclusion/Exclusion Criteria | - 60 years of age or older - No current major psychiatric or neurologic disease - No history of stroke or seizures - All other medical conditions controlled by stable therapy |
| Study Intervention and Planned Use | The experimental intervention will be delivered using the Vielight Neuro Gamma device. The device uses 5 light emitting diodes (810nm wavelength). Four diodes provide near-infrared energy transcranially, while the last does so intranasally, all targeting regions of the Default Mode Network. No significant heat is generated, allowing for a sham device which will be indistinguishable from the intervention to both the subjects and EEG technician. Devices will be utilized concurrently with EEG recording of subject at rest. The devices will be used in a randomized crossover design within the single study visit with the same EEG recordings to be obtained under both sham and active conditions. |
| Study Procedures | 1. Informed Consent 2. Eligibility Assessment 3. First EEG Recording 4. One week washout period 5. Second EEG Recording |
| Primary Endpoint | Change from baseline in overall power spectral density between active and sham session |
| Statistical Methodology | Repeated measures ANOVA with treatment as within subject measure |

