## Study Design

This is a non-randomized prospective experimental study.

Study Procedures are as follows:

1. Informed Consent
2. Eligibility Assessment
3. First EEG Recording
4. One week washout period
5. Second EEG Recording

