## Eligibility of Subjects, Exclusions, Missing Data, and Removal of Subjects

All subjects responding to the advertisements are potential study candidates and will be screened for eligibility. Every effort will be made to ensure eligibility of the subjects prior to study enrollment. Subjects who do not meet all inclusion/exclusion criteria will not be enrolled or followed in the study. Subjects for whom no data was acquired due to technical failures or those that withdraw consent will be excluded from analysis. Subjects for whom only partial data was acquired will be included in all possible analysis.

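### The primary ANOVA names treatment alone, so a visit effect on the change score would enter the residual and, if the sequences are unequal, the device estimate

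*Protocol*

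**What the plan says.** Section 6.1 (Planned Analysis) defines the primary endpoint as "change from baseline in overall power spectral density between active and sham session" and states that "a repeated measures ANOVA with treatment as the within-subject measure will be utilized". The Synopsis row on statistical methodology gives the same model: "Repeated measures ANOVA with treatment as within subject measure". Neither place names period, sequence or visit order, and nothing elsewhere in the protocol brings them into the analysis.

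The procedures list two EEG recordings separated by a "One week washout period". The visits are not identical: "The second study visit will be a replication of Part C of the first visit", so consent, eligibility review and the MMSE precede the EEG at visit 1 only.

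The protocol contradicts itself on allocation. The Synopsis says "The devices will be used in a randomized crossover design within the single study visit", while the Study Design section says "This is a non-randomized prospective experimental study". No sequence ratio or balancing method is given. The Synopsis sentence also places both conditions in one visit; I follow the listed procedures, which have two.

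**The concern.** In a two-period crossover each subject contributes one active-minus-sham difference. If response differs between visits for reasons unrelated to the device, that difference is shifted one way in subjects who receive active first and the other way in those who receive it second. A model without period treats the shift as noise when the two orders are equally frequent, and leaves part of it in the device estimate when they are not.

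A visit effect is plausible here. The first recording follows the consent and screening procedures and is the subject's first in this study; the second is neither. What is at stake is the power of the one primary test and the accuracy of the effect size that, according to Section 6.2, is to inform later confirmatory studies.

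**Working it through.** **Inputs from the protocol.** N=20 (Section 6.2); two conditions in two sessions; treatment the only model term named (Section 6.1, Synopsis). Section 6.2 bases N on literature precedent and gives no alpha, power, effect size or SD, so there is no power figure to reproduce.

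**Assumptions not in the documents.** Two-sided alpha 5%. A true effect d of 0.66 SD of the paired difference, which is the value giving 80% power for a paired t-test at N=20. A visit-2-minus-visit-1 effect p on the change score of 0, 0.25, 0.5 or 0.75 of the same SD.

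**Step 1: the stated model.** With two conditions, a repeated measures ANOVA with treatment alone is the paired t-test on the difference D, with 19 degrees of freedom.

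**Step 2: what a period effect does to D.** Let n1 subjects receive active at visit 2 and n2 at visit 1. The expected D is d+p in the first group and d-p in the second. With the SD of D within a sequence set to 1:

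- bias of the mean difference = p(n1-n2)/N
- expected sample variance of D = 1 + p² × 4n1n2/(N(N-1))

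For p=0.5:

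- 10:10: bias 0; variance 1 + 0.25 × 400/380 = 1.26
- 12:8: bias 0.5 × 4/20 = 0.10 SD
- 13:7: bias 0.5 × 6/20 = 0.15 SD

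**Step 3: with period fitted.** The estimate is the mean of the two sequence means, on 18 degrees of freedom. Bias is 0 and size 5% whatever p is. The non-centrality is 0.66 × √20 × √(4n1n2/N²). The factor 4n1n2/N² is 1.00 at 10:10, 0.96 at 12:8 and 0.91 at 13:7, which gives power of 79.8%, 78% and 76%.

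**Step 4: size and power of the stated model.** Simulated with at least 100,000 trials per case; figures vary between runs by up to about one percentage point.

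| Split | p (SD) | Size | Power, treatment only | Power, period fitted |
|---|---|---|---|---|
| 10:10 | 0 | 5.0% | 80% | 80% |
| 10:10 | 0.25 | 4.2% | 78% | 80% |
| 10:10 | 0.5 | 2.9% | 72% | 80% |
| 10:10 | 0.75 | 1.5% | 62% | 80% |
| 12:8 | 0.5 | 4.4% | 57% or 85% | 78% |
| 13:7 | 0.5 | 6.5% | 50% or 89% | 76% |

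Where two powers are shown, the lower applies when the bias opposes the device effect and the higher when it favours it. In the second case the estimate is also overstated.

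**Step 5: how often such splits occur.** If 20 subjects were allocated by simple 1:1 randomization, the split would be 12:8 or worse with probability 50% and 13:7 or worse with probability 26%.

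**Step 6: averaged over simple random allocation.** Expected bias is zero. For p = 0.25, 0.5 and 0.75 the size of the paired test stays at about 5%, and its power is 78%, 71% and 61%.

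**Step 7: a single fixed order.** With n1=20 and n2=0 the bias is p × 20/20 = p, the whole period effect. Treatment and period are then fully confounded and no model term can separate them.

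**The case against.** The strongest reply is that the protocol names treatment as the within-subject measure without ruling out other terms. Sequence is a between-subject factor, and an ANOVA with treatment within and sequence between would give the period-adjusted test; an unseen SAP might add it. That is fair as far as it goes. But the model is stated twice with nothing else named, so a SAP that followed the protocol literally would leave period out.

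Several stronger readings are tempting and should not be drawn:

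- **That every session-order effect matters.** The endpoint is a change from a baseline recorded in the same session. A shift common to that baseline and the later recordings cancels, as does a pure between-sequence difference. Only a visit effect on the change itself does harm.
- **That the primary test is invalid.** The bias is conditional on the split that occurs. At 10:10 and 12:8 with p=0.5 the test is conservative, not inflated, and averaged over random allocation its size is about 5%.
- **That a confirmatory test is being compromised.** Section 6.2 describes an initial study preceding confirmatory ones and claims no power. The 80% benchmark is mine. The reply does not remove the point, because a distorted estimate or residual SD would carry into the later sample sizes.
- **That the ANOVA conflicts with the missing-data rule in Section 6.3.** That section says "Subjects for whom only partial data was acquired will be included in all possible analysis". The wording already allows for analyses that a partial record cannot enter, so there is no contradiction.

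**Conclusion.** The point stands as a recommendation of moderate weight. As written, the primary model has no period term in a design where a visit effect on the change score is plausible. The algebra is certain; the size of the harm is not, because p, the true effect and the sequence split are all assumed.

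With balanced sequences the loss is about 2 points of power at p=0.25 SD, 8 at 0.5 and 18 at 0.75, and nothing at p=0. With a realised imbalance, the estimate is also displaced by p(n1-n2)/N in a direction that cannot be known in advance. Under random allocation the overall effect is mainly lost power. If the order were fixed, as the description of the study as non-randomized would permit, the problem would lie in the design and the model change below would not cure it.

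**What to change.** In Section 6.1 and in the Synopsis, specify the primary analysis as a linear mixed model for change from same-session baseline, with fixed effects for treatment and period and a random subject effect, reporting the treatment effect with its 95% CI. A sequence term is optional.

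Also reconcile the Synopsis with the Study Design section so that the protocol says plainly that both orders are used and how subjects are allocated to them. Without both orders the period term cannot be estimated separately from treatment.

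The cost is a few lines of text and one residual degree of freedom (19 to 18; critical t 2.093 to 2.101). If there is in fact no period effect, the term costs about 0.2 points of power at 10:10, 2 at 12:8 and 4 at 13:7.
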